### Study intervention

All study patients will receive usual physiotherapy interventions while in intensive care. Physiotherapy interventions will include (but are not limited to): respiratory physiotherapy, physical rehabilitation exercise interventions including sitting on the edge of the bed, sit to stand transfers, sitting out of bed and walking. Usual care physiotherapy interventions will be prioritised over the in-bed cycling intervention. Safety guidelines (see box 1) will be used to determine if the intervention group patients are able to complete an additional daily 30 min progressive lower limb in-bed cycling using a bedside cycle ergometer (MOTOmed Letto 2). The lead physiotherapist ([name]) who has over 10 years of experience in rehabilitative exercise with patients with critical illness will primarily conduct the majority of in-bed cycling sessions. He has been trained by industry cycle ergometry representatives and has over 5 years of experience conducting in-bed cycling sessions with patients with critical illness. Experienced ICU physiotherapists trained in conducting in-bed cycling sessions may conduct the in-bed cycling sessions if the lead physiotherapist is unavailable. During the in-bed cycling exercise interventions, the patients’ vital signs will be monitored. If the intervention group patients are in a state of low arousal or sedated, they will cycle continuously and passively at the default passive speed of the cycle ergometer (20 revolutions per minute) for 30 min. When the participant is following commands, the clinician will verbally encourage the patient to complete in-bed cycling sessions actively for a duration of 30 min. Once the patient can cycle actively, the resistance applied by the cycle ergometer will be adjusted to facilitate patient intensity between 3 and 5 using the visual Borg scale rate of perceived exertion (category ratio 10),^14^ within the specified safety guidelines. An exercise intensity of 3–5 on the Borg rate of perceived exertion scale has been shown to be safe and feasible with patients with critical illness.^15^ This will enable the patient to cycle in-bed either passively or actively with assistance from the cycle ergometer. If a patient unexpectedly commences active cycling, the additional active in-bed cycling safety criteria will become relevant. If the patients are deemed unsuitable to continue active in-bed cycling, they will be asked to resume passive cycling. If the patient continues to actively cycle, the session will be ceased. The in-bed cycling sessions will continue until the patient completes a minimum of five in-bed cycling sessions, unless the patient is discharged from hospital prior to completing five sessions. The intervention will continue in the acute hospital ward if the patient is discharged from ICU prior to completing five in-bed cycling sessions. While the patient remains in ICU, in-bed cycling sessions will continue (up to 7 days/week), up to 28 days post-ICU admission. This frequency is congruent with usual physiotherapy services that can provide rehabilitative exercise interventions to ICU patients up to 7 days/week. Patients randomised to the usual care arm do not routinely complete in-bed cycling sessions during their hospitalisation. Any deviations from the planned protocol will be recorded to enable appropriate intervention description and, if indicated, a per-protocol analysis (in addition to the primary intention-to-treat analysis).

Participants will not be coerced to complete any intervention or outcome measure. Participants may be discharged home from the participating acute hospital before they have completed outcome measures at each assessment time point. If this occurs, participants will be asked to return to the hospital to enable the remaining outcome measures to be completed and expenses related to taxi or parking costs will be reimbursed.

### Outcomes

Table 2 provides a summary of the outcome measures. The primary outcome is the percentage of change in rectus femoris CSA measured at baseline (within 24 hours of study enrolment) and day 10 (post study enrolment), measured by a blinded assessor. The participants will be assessed to examine whether there is a between-group difference in the amount of rectus femoris CSA atrophy. The authors anticipate that less rectus femoris CSA atrophy will be observed among the in-bed cycling group. Day 10 post study enrolment has been chosen as the primary endpoint to enable comparison with previously published data on acute skeletal muscle wasting in patients with critical illness and consistent with this previously reported time frame of observed muscle wasting.^1^ Secondary outcome measures in the CYCLIST (Critical Care Cycling Study) are muscle strength, physical function, cognition, quality of life and acceptability of intervention.

**Table 2 T2:** Descriptions of outcome measures for CYCLIST RCT

Assessment component	Outcome measure	Description
Muscle morphology	Ultrasound	RF CSA, AP thickness of RF and VI. Measured in triplicate on right anterior thigh one-third distance from superior patella to ASIS. Patient positioned in supine, 30º head elevation^27^
Muscle strength	MRC sum score	Standardised sum of 12 MMTs, 3 MMTs per limb Score ≤48 indicative of ICU-acquired weakness^28^
	Handgrip strength dynamometry	Triplicate bilateral measurement using a Jamar Digital Dynamometer (Lafayette) with seated patient^29^
Physical function	ICU Mobility Scale	Best level of function achieved in ICU using an 11-point ordinal scale^30^
	FSS-ICU	Patients’ function measured an 8-point ordinal scale^31 32^
	Functional milestones	Time to achieve functional milestones: sit out of bed, time to stand, mobilise with assistance and mobilise independently
	6 min walk test	Submaximal endurance test of distance walked by a patient in 6 min^33^
Cognition	CAM-ICU	Incidence and recorded episodes of acute delirium^34^
Quality of life	EQ-5D-5L	EQ-5D-5L^35^
Intervention acceptability	Customised questionnaires	Questionnaire about the acceptability of the in-bed cycling intervention

AP, anterior posterior; ASIS, anterior superior iliac crest; CAM-ICU, Confusion Assessment Method for the Intensive Care Unit; CSA, cross-sectional area; CYCLIST, Critical Care Cycling Study; EQ-5D-5L, EuroQol Five Dimensions questionnaire Five Levels scale; FSS-ICU, Functional Status Score for the Intensive Care Unit; ICU, intensive care unit; MMT, manual muscle test; MRC, Medical Research Council; RCT, randomised controlled trial; RF, rectus femoris; VI, vastus intermedius.

Demographic information such as age, gender and diagnostic code will be collected. Illness-related information including length of mechanical ventilation, ICU length of stay (LOS)/hospital LOS and discharge destination, illness severity (Acute Physiology and Chronic Health Evaluation III,^16^ Sequential Organ Failure Assessment^17^ score), premorbid comorbidities, neuromuscular blockade and sedation medications administered, nutrition received, cumulative fluid balance, patient’s height and weight, and body mass index will also be collected.

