### Participants

The study aims to recruit 68 participants. Adult patients expected to require at least 48 hours of mechanical ventilation will be recruited, with the inclusion and exclusion criteria listed in table 1. Criteria to guide when to discontinue or not deliver an intervention are listed in box 1. Participants can be recruited into the study and baseline sonography measures performed if a patient does not currently meet the in-bed cycling safety criteria in box 1 (but are considered by their treating clinical team to be likely to meet the criteria within their stay in ICU).

**Table 1 T1:** Inclusion and exclusion criteria

Inclusion	Exclusion
Expected to require more than 48 hours of invasive mechanical ventilation	Pre-existing condition that is likely to impair mobility/mobility assessment (ie, significant neurological, musculoskeletal, cognitive or mental health disorder)
Able to provide consent or have a family member consent on their behalf	Neuromuscular disorder or acute primary brain lesion (ie, traumatic brain injury, intracranial haemorrhage, stroke or hypoxic brain injury)
Enrolled into the study within 96 hours of ICU admission	Injuries precluding cycle ergometry (ie, spinal/pelvic/lower limb orthopaedic injuries/open abdominal wound)
Expected to remain in ICU for more than 48 hours following study enrolment	Obesity >135 kg (MOTOmed Letto 2 maximum rated weight capacity)
	Uncontrolled seizures or status epilepticus
	Dire prognosis (ie, unlikely to survive the current admission)
	Pregnancy
	Children and/or young people (ie, <18 years)

ICU, intensive care unit.

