Box 1Safety guidelinesActive or passive exercise should not be delivered if:Clinician’s opinion that patient’s condition is unstableResting HR<40 or >120 bpm or new arrhythmiaEvidence of coronary ischaemia, for example, chest pain or ECG changesMAP<60 or SBP>200 mm HgSpO_2_<90%RASS≥2Wounds of leg, pelvis or lumbar spine precluding cycle ergometryEvidence of active bleeding or coagulation disorder: INR>1.8, PLT<50 000/µL*Femoral vascular access†, for example, dialysis catheter, IABP, ECMO or lower limb arterial line‡Acute DVT or PEActive exercise should not be delivered if:>20 µg/min of norepinephrine or comparable inotropic or vasopressor supportFiO_2_>0.55 or PEEP>10 cmH2ORR>30 with adequate ventilatory supportTemperature >39°CStopping criteria: active or passive exercise should cease if:HR<50 or >140 bpm, or new arrhythmia develops (including ventricular ectopic or new-onset AF)Evidence of coronary ischaemia, for example, chest pain or ECG changesMAP<60 mm HgSBP>200 mm HgClinical signs of cardiorespiratory distressSpO_2_<90% for more than 1 minPatient’s request to stop therapy*Values outside this range would be tolerated if patient is therapeutically anticoagulated.†Other than femoral central line.‡If a femoral vascular access is inserted unilaterally the contralateral leg may be cycled unilaterally.AF, atrial fibrillation; bpm, beats per minute; DVT, deep vein thrombosis; ECMO, extracorporeal membrane oxygenation; FiO_2_, fraction of inspired oxygen; HR, heart rate; IABP, intra-aortic balloon pump; INR, international normalised ratio; MAP, mean arterial pressure; PE, pulmonary embolism; PEEP, positive end expiratory pressure; PLT, platelets; RASS, Richmond Agitation Sedation Score; RR, respiratory rate; SBP, systolic blood pressure; SpO_2_, saturation of peripheral oxygen.

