### Analysis

Data will be analysed and reported using intention-to-treat principles (primary analysis). A per-protocol analysis will be conducted to assist in determining the efficacy of the in-bed cycling protocol if variation from the planned protocol occurs for a substantial proportion of patients. The per-protocol analysis will include only patients who adhered to the protocol and received at least 80% of training sessions (minimum of four sessions).

Descriptive statistics and generalised linear mixed models (that can adjust for baseline status) will be used to examine the effect of group allocation (intervention vs usual care) on the primary and secondary outcomes.^18^ As this is a randomised trial, we do not plan to adjust for potential confounders (eg, age, gender, comorbidities), but will compare the characteristics of the sample by treatment group and may adjust if a potential confounder differs greatly between groups.

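### The primary scan is fixed to the right thigh, but Box 1 permits left-leg-only cycling, so some cycling-arm patients may be measured on a leg that was not cycled

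*Protocol article*

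**What the plan says.** **Scanned leg.** Table 2 (Outcomes) sets the ultrasound site for rectus femoris cross-sectional area: "Measured in triplicate on right anterior thigh one-third distance from superior patella to ASIS". No alternative side is given. This scan feeds the primary endpoint: "The primary outcome is the percentage of change in rectus femoris CSA measured at baseline (within 24 hours of study enrolment) and day 10".

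**Cycled leg.** Box 1 lists conditions under which neither active nor passive exercise is to be delivered. One is "Femoral vascular access†, for example, dialysis catheter, IABP, ECMO or lower limb arterial line". Two footnotes qualify it. The first exempts one kind of line: "Other than femoral central line". The second covers access on one side: "If a femoral vascular access is inserted unilaterally the contralateral leg may be cycled unilaterally".

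**Who can be enrolled.** Table 1 does not exclude femoral access. The Participants section adds: "Participants can be recruited into the study and baseline sonography measures performed if a patient does not currently meet the in-bed cycling safety criteria", provided the treating team thinks the patient likely to meet the criteria during the ICU stay.

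**Analysis.** The Analysis section states: "Data will be analysed and reported using intention-to-treat principles (primary analysis". A per-protocol analysis, run if a substantial proportion of patients depart from the protocol, keeps patients who adhered and "received at least 80% of training sessions (minimum of four sessions". Neither this rule nor the list of secondary analyses in Box 2 refers to the leg that was cycled.

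**The concern.** The objective is to learn whether cycling slows wasting of the rectus femoris, so the muscle measured should be one that was exercised. The two rules were written separately and nothing links them. With non-exempt access in the right groin only, the plan as written allows left-leg sessions while every scan is taken on the right.

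The usual-care arm is unaffected, because it is not cycled. Any mismatch therefore falls in one arm and pulls the difference toward zero. The per-protocol analysis is meant to speak to efficacy, but it does not screen these patients out: one-leg cycling is permitted by Box 1, so it is not on its face a deviation, and the threshold is a count of sessions. A null result would then be harder to read, since it could reflect either no effect of cycling or measurement of an untrained muscle.

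If the left thigh is never scanned, no later analysis can recover the missing measurement. The scanned side therefore has to be settled before data accrue.

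**Working it through.** **Step 1. Can the mismatch arise under the rules as written?** It needs all of the following:
- femoral access of a non-exempt kind (a femoral central line does not count);
- access on the right side only;
- access in place during at least some sessions before day 10;
- a decision to cycle the left leg alone, which the footnote permits but does not require.

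No rule excludes this combination, and the footnote shows that one-leg cycling was foreseen. The documents give no frequency for any of the conditions.

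**Step 2. Reproduce the plan's figure.** Inputs from the Sample size section: difference 2.9, SD 6, within-patient correlation 0.5, type I error 0.05 (taken as two-sided, which the text does not state), 80% power, 20% dropout, 34 per group recruited and about 27 completing.

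The variance of a baseline-adjusted average of *m* follow-up scans is SD² × [(1 + (m − 1)ρ)/m − ρ²]. For the scans at days 3, 7 and 10, m = 3:
- bracket = (1 + 2 × 0.5)/3 − 0.25 = 0.4167
- effective SD = 6 × √0.4167 = 3.873
- n per group = 2 × 3.873² × (1.960 + 0.842)² / 2.9² = 28
- at 27 per group, standard error = 3.873 × √(2/27) = 1.054 and 2.9/1.054 = 2.75, giving power 78.6% (normal approximation) or 77.0% (t distribution)

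This is close to the stated 27 and 80%, so it serves as the reference. It is also the most favourable reading for the plan. With day 10 alone and adjustment for baseline, the effective SD is 6 × √0.75 = 5.196, n is 51 per group, and power at 27 is 54%.

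**Step 3. Worst-case dilution.** Let *f* be the share of the cycling arm whose right leg is never cycled before day 10, and assume no effect at all on the uncycled thigh. The expected difference is then 2.9 × (1 − f). The values of *f* are assumptions.

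| f | Expected difference | Power, 27 per group, three-scan average (t – normal) | Power, 27 per group, day 10 alone, baseline-adjusted (normal) |
|---|---|---|---|
| 0 | 2.90 | 77.0–78.6% | 53.6% |
| 5% | 2.76 | 72.7–74.3% | 49.5% |
| 10% | 2.61 | 68.1–69.7% | 45.4% |
| 20% | 2.32 | 57.9–59.5% | 37.5% |

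**Step 4. A milder scenario.** Suppose 20% of the arm have unilateral non-exempt access, half of it right-sided and in place for half the sessions, and suppose the lost effect is proportional to the sessions missed. The effective share is 0.20 × 0.5 × 0.5 = 5%, which is the second row. To reach f = 10% to 20% with the sides equally likely, 20% to 40% of the arm would need such access throughout.

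**The case against.** The strongest reply is that the problem is only conditional and may be small. A reader might infer from the two rules that some patients will certainly be measured on an untrained leg. The documents do not support that. Central lines are exempt, one-leg cycling is optional, and the number affected among about 27 completers could be zero. This stands, and the point is worded accordingly.

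A reader might also infer that affected patients show no training effect at all. That needs the right leg to go uncycled throughout and the benefit to be purely local. Sessions are daily, a line may be removed, and both legs can then be cycled. The Background also suggests that exercise may act by moderating inflammation, which need not be confined to one leg. This stands too: the table in the working gives upper limits.

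A third tempting reading is that the primary comparison is biased or invalid. It is not. Intention to treat still estimates the effect of the cycling policy as delivered, restrictions included, and the error runs only toward no difference.

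Finally, the article does not say how a one-leg session counts toward the per-protocol threshold, and its session form is not shown. The leg cycled may already be recorded, and a sensitivity analysis may sit in an unseen analysis plan. That is fair for those two items. It does not answer the main point, because the article itself fixes the scanned side with no exception.

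**Conclusion.** The concern holds in conditional form. The fixed right-thigh scan and the one-leg cycling footnote are not reconciled, so following the plan as written may measure a muscle that was not cycled. The effect is conservative: dilution of the intention-to-treat estimate, which the per-protocol rule as written does not remove.

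The size is unknown. The worst-case loss for 5% to 20% affected is about 4 to 19 percentage points of power. That rests on assumed shares, on no effect in the uncycled thigh, on a right leg never cycled before day 10, and on the three-scan average rather than the day-10 endpoint that the Outcomes section names. The true loss is probably smaller. Severity is minor to moderate: a cheap improvement worth making, not a flaw that undermines the trial.

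**What to change.** Change measurement and analysis only; the cycling rule in Box 1 is not in question here.

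1. **Scanned side.** Choose it at baseline, before allocation is revealed, by the same rule in both arms: right thigh unless a right-sided non-exempt femoral device or other right-leg restriction is present, in which case left. Keep that side for all scans. The Randomisation section already places baseline data collection before allocation is revealed, so the order of work does not change.
2. **Session record.** Add a field for the leg or legs cycled in each session, if the form does not already have one.
3. **Sensitivity analysis.** Prespecify one for patients whose scanned leg was not cycled. It is needed because a baseline rule cannot cover lines inserted later.
4. **Per-protocol set.** A count restricted to sessions that cycled the scanned leg should be at most a supplementary analysis. It adds selection after randomisation in one arm only.

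The cost is one sentence in the ultrasound procedure, one field on the form and one prespecified analysis, with no extra scans or staff. The downside is that a few left-thigh series are mixed with right-thigh ones, though each is compared with its own baseline. Scanning both thighs in everyone would also work, at greater cost.

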### Sample size

Based on the repeated measures design, this study will have 80% power to detect a between-group difference of 2.9% on our primary outcome (change in rectus femoris CSA) between the intervention and usual care participants (assuming type I error 0.05, SD of 6%, and within-patient correlation of 0.5 between assessments, and after accounting for an up to 20% dropout rate including in-hospital mortality). A total of 68 patients (34 in each group) will be recruited into the study. With a dropout rate of up to 20%, this would represent approximately 27 participants completing the trial in each group. It is noteworthy that some of the assumptions for this calculation have been made in the absence of prior RCT data. There is some risk that the observed trial data may not fit these assumptions (eg, discrepancies in SD or within-patient correlation between the repeated measures), and the power of the study may differ from this a priori sample size estimate.

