### Randomisation

Patients will be individually randomised in a 1:1 ratio to either intervention or usual care group. Blocking (random block sizes) will be used to help balance the groups. An investigator not involved in the screening, consenting, allocation or assessment processes will use computerised random number generation to create the randomisation sequence. A randomisation sequence will be uploaded onto the Research Electronic Data Capture (REDCap) secure web-based computer application.^13^ The REDCap randomisation module will reveal the group allocation of each patient to the intervention coordinator after a patient’s baseline data have been collected.

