CYCLIST is a phase IIb RCT that is powered to investigate if the early application of an additional in-bed cycling intervention is able to reduce the rate of skeletal muscle atrophy of patients’ quadriceps muscle during and immediately following a period of critical illness, in comparison to usual care. Secondary outcomes evaluated in this study will assist sample size calculations for future studies to assess for efficacy of functional outcomes. The study will also aid planning of future rehabilitation-based clinical trials with regard to rate of participant recruitment. The investigators are planning to meet at the completion of the study to facilitate reflection on aspects of the study that could be improved and to consider whether a definitive phase III RCT is warranted. This will include consideration of the evidence of effect on primary and secondary outcomes, participant recruitment and adherence to the in-bed cycling protocol and rate, as well as acceptability of the intervention.

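### The 80% power for a 2.9-point difference does not apply to the day-10 primary outcome; the stated inputs give about 41%, or 52% with baseline adjustment.

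*Protocol article*

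**What the plan says.** The Sample size section bases its calculation on a repeated measures design and states that "this study will have 80% power to detect a between-group difference of 2.9% on our primary outcome (change in rectus femoris CSA"). The inputs are given as "assuming type I error 0.05, SD of 6%, and within-patient correlation of 0.5 between assessments". It recruits 68 patients, 34 per arm, and says that up to 20% dropout is already allowed for: "this would represent approximately 27 participants completing the trial in each group".

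The Outcomes section fixes the primary outcome as the percentage change in rectus femoris cross-sectional area between baseline and day 10: "Day 10 post study enrolment has been chosen as the primary endpoint". The Abstract agrees. Box 2 lists muscle wasting at day 3, day 7 and one week after ICU discharge among the secondary analyses. The Analysis section uses generalised linear mixed models that can adjust for baseline.

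The Discussion then says that "CYCLIST is a phase IIb RCT that is powered to investigate if the early application" of in-bed cycling reduces the rate of quadriceps atrophy.

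**The concern.** The power sentence refers to the primary outcome, which is one comparison at one time point. An SD of 6 and 27 patients per arm look too few to detect a difference of less than half an SD (2.9/6 = 0.48) with 80% power. The stated correlation of 0.5 does not rescue it, because at 0.5 a change score is exactly as variable as a single measurement.

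If the 80% belongs to some other quantity, readers will trust the day-10 test more than they should. The Discussion says that evidence of effect on the primary outcome will feed into the decision on a phase III trial. A null day-10 result could then be read as evidence against a 2.9-point effect that the test had roughly an even chance, or less, of detecting.

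**Working it through.** **Inputs.** From Sample size: difference 2.9, SD 6, within-patient correlation ρ = 0.5, type I error 0.05, 34 recruited and about 27 completing per arm. From Randomisation: 1:1 allocation. Sidedness is not stated, so two-sided is assumed.

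**Method.** Let f be the variance factor, so the effective SD is s = 6√f and the standard error of the group difference is s√(2/n). For a baseline and m follow-ups with equal correlation ρ:

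- change score, one follow-up: f = 2(1 − ρ) = 1.00, s = 6.00
- baseline-adjusted, m follow-ups averaged: f = (1 + (m − 1)ρ)/m − ρ²
  - m = 1: f = 0.75, s = 5.20
  - m = 3: f = 2/3 − 1/4 = 0.4167, s = 3.87

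In the normal approximation the detectable difference is (1.960 + 0.842) × s√(2/n). Noncentral-t figures are slightly less favourable.

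**Step 1: reproduce the plan's figure.** Baseline-adjusted mean of three follow-ups (Table 3 schedules scans at days 3, 7 and 10):

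- n = 28: 2.802 × 3.873 × √(2/28) = 2.90, power 80.0% (normal)
- n = 27: 2.802 × 3.873 × √(2/27) = 2.95, power 78.6% (normal); 3.01 and 77.0% (t)

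Other averages also come close. Four follow-ups at 27 per arm give 82.6% (normal) or 81.2% (t). Two follow-ups with all 34 per arm give 2.88 and 80.5% (normal), but that ignores the dropout said to be accounted for. All of these average over scans.

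**Step 2: the day-10 outcome as defined** (t-based).

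| Day-10 analysis | n per arm | SE | Power at 2.9 | Detectable at 80% |
|---|---|---|---|---|
| Change score, s = 6.00 | 27 | 1.63 | 41.4% | 4.66 |
| Baseline-adjusted, s = 5.20 | 27 | 1.41 | 52.1% | 4.04 |
| Change score | 34 | 1.46 | 50.2% | 4.14 |
| Baseline-adjusted | 34 | 1.26 | 62.1% | 3.58 |

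The normal approximation at 27 per arm gives 42.7% and 53.6%, with detectable differences of 4.57 and 3.96.

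**Step 3: what 80% at 2.9 would take.** It needs 69 evaluable per arm (change) or 52 (adjusted), t-based. With 20% dropout that is 69/0.8 = 86.25, so 87 recruited per arm, or 52/0.8 = 65 per arm. Alternatively, at 27 per arm, the correlation would have to be about 0.81 (change) or 0.78 (adjusted) instead of 0.5.

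**Step 4: sensitivity to reading.**

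- *Meaning of the SD.* If 6% is the SD of one assessment, the change SD is 6√(2 × 0.5) = 6. If it is the SD of the change, it is 6 directly. The 41% is the same either way. The 52% needs 0.5 to be the correlation between baseline and day 10.
- *Correlation among percentage changes.* If 0.5 is the correlation between the percentage changes at days 3, 7 and 10, their mean has s = 6√(2/3) = 4.90 and a detectable difference of 3.7 at 27 per arm. That reading does not give 2.9 either.
- *One-sided 0.05.* Power is 55% (change) or 66% (adjusted), normal approximation.
- *Mixed model on days 0, 3, 7 and 10.* With complete data and a separate effect at each time, the day-10 contrast equals the single-scan adjusted analysis, about 52%. Imposing an effect that grows linearly to day 10 and equal baseline means gives SE 1.31, a detectable difference of 3.7 and power of about 60%.

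**The case against.** The strongest reply is that the calculation contains no slip. The section announces a repeated measures design and gives a correlation between assessments, and Table 3 has three follow-up scans up to day 10. A baseline-adjusted average of those scans gives 2.9 to within rounding of the completer number. **This stands**: the likely fault is a mismatch between the quantity that was powered and the endpoint that was named. It also means that the 77% to 79% at exactly 27 per arm is rounding, not a second error.

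It does not save the sentence. The article attaches the figure to "our" primary outcome, fixes that at day 10, and puts the day 3 and day 7 scans among the secondary analyses. Nowhere does it name an average as primary. While muscle is being lost progressively, an average that includes day 3 is also not the same quantity as the loss by day 10.

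Two further replies carry less weight:

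- The section warns that power may differ if the SD or correlation is not as assumed. The shortfall here arises when both are exactly as assumed.
- The Discussion speaks of the rate of atrophy and does not name day 10. That is fair, so the claim there needs qualifying, not necessarily deleting.

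The formula may be set out in a fuller document that is not shown, but that would not change what the article says about the outcome it names.

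**Conclusion.** The concern holds. For the day-10 outcome, power at 2.9 points is 41% (change score) or 52% (baseline-adjusted), against the stated 80%. That is an overstatement of about 28 to 39 percentage points. The most favourable mixed-model reading examined, with a linear effect and equal baselines, reaches about 60%.

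These results assume a two-sided 0.05 test, SD 6, 27 evaluable per arm, and, for the adjusted figures, a correlation of 0.5 between scans including baseline. That the authors averaged three scans is inferred from the close numerical match and from Table 3; the article does not say so.

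**What to change.** Choose one of two routes and state it in the Sample size section.

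1. **Keep day 10 as primary and keep n = 68.** Suggested wording: *With 27 evaluable patients per arm, the day-10 comparison has 80% power for a difference of about 4.7 percentage points (4.0 if adjusted for baseline with correlation 0.5); power for 2.9 points is about 41% (52% adjusted).*
2. **If the averaged effect was intended,** name the baseline-adjusted mean over days 3, 7 and 10 as the primary estimand in Abstract, Outcomes, Sample size and Analysis. State a detectable difference of about 3.0 points at 27 per arm, and revise Box 2 to match.

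In either case, say whether the 6% is the SD of a single assessment or of the percentage change, which pairs of assessments the 0.5 describes, and whether the test is two-sided. Qualify the Discussion's statement that the trial is powered, so that it names the outcome and the detectable difference.

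The first route costs only wording and a less favourable figure. The second changes the primary estimand, so it should be settled before outcome data are seen and declared as a protocol modification. Keeping both day 10 and 2.9 points at 80% would instead require 65 to 87 recruited per arm.
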